#### *Primary and Secondary Outcomes*

The primary outcome will be **clinical malaria**, defined (according to WHO criteria) as parasitemia (malaria parasites detected on a blood smear) of any density plus history of fever (within 48 hours) or axillary temperature  $>37.5^{\circ}\text{C}$ . Criteria for clinical malaria will be taken from the UNICEF Case Management Series, entitled, "Promoting Rational Use of Drugs and Correct Case Management in Basic Health Services – Malaria Prevention and Treatment" published by UNICEF's Programme Division in cooperation with the World Health Organization in 2000. To distinguish unique malaria episodes, treatment will be supervised and follow-up blood smears will be collected from the child as described below in Section 5.2(c).

Secondary outcomes will include: (i) changes in anemia status; (ii) the severity of the clinical malaria (based on level of parasitemia); (iii) cerebral malaria; (iv) hospitalization (from any cause) (v) death; (vi) pneumonia; (vii) diarrhea and dehydration.

*Subjects/study population*

Infants and young children (6-24 months of age), living in the Brong Ahafo Region of northern Ghana, will be included in the study if, at baseline, they are ingesting weaning foods in addition to breastmilk; free from malaria or other major illness; afebrile; living in the study area for the duration of the intervention and follow-up period; and if parental consent is obtained. Inclusion of a child into the study will proceed after the possible risks and benefits are discussed with the parents (in the appropriate local language), and a signed consent is obtained. The exclusion criteria are as follows: severe anemia (hemoglobin <70g/L), weight-for-height <-3 z-score (severe wasting), kwashiorkor (defined as evidence of edema), congenital abnormality, treatment with iron supplements in the past 6 months, or any chronic illness. Children that are severely anemic (Hb<70 g/L) and/or have symptoms of clinical malaria will be excluded from entry to the study and referred to the local health provider for treatment according to Ghana Ministry of Health guidelines.

*Sample Size*

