a) *Baseline:* After consent is provided, subjects will be screened for anemia (based on hemoglobin) and parasitemia. Enough blood will be taken to determine ferritin (SF), C-reactive protein (CRP), serum transferrin receptor (TfR) and zinc protoporphyrin (ZnPP). Those who are severely anemic (Hb <70 g/L), or have clinical signs of infection (including malaria) will be referred to the study clinician who will offer the child the standard care, as defined by the Ghana Ministry of Health. All other children will be enrolled and randomized to either the iron (Fe) or placebo (P) group. The child's weight and length measurements will be recorded, as well as any relevant demographic (age, gender) and historical health information (birth weight, immunization status, and previous hospitalizations). Caregivers will also be asked to provide information regarding their usual feeding practices and health-seeking behaviours. All households will be provided with a treated bed net and a supply of powdered fortificant with oral instructions on how to use each.

*b) Monitoring visits:* Field researchers will visit each subject at their home every week in the first month of the study and at 4 week intervals for the next 4 months. At each visit, the field researcher will conduct a health assessment (including axillary temperature) and collect information on feeding history, supplement compliance, bed net use and morbidity. At the initial weekly visits, 7 new sachets will be provided, and then at the start of the second month, 30 new sachets will be provided to last for a month. Clear instructions for storage and administration of sachets will be provided to families. All used and unused sachets will be counted and recorded. It has been our experience in other similar studies in Ghana and elsewhere that by providing pre-emptive information on the impact of the fortificant to parents (like telling parents that stools will darken from the iron, and that children will become more active and have enhanced appetites), the adherence to the use of the sachets is generally in the range of 70 – 98%. We will provide this pre-emptive information in the current study.

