*c) Follow up:* At the end of 5 months, subjects will again be screened for anemia, ferritin, CRP, serum transferrin receptor, zinc protoporphyrin and a blood smear for their malaria status. The subjects will be weighed and measured, and caregivers will again be asked about feeding history, supplement use, and bed net use. Any remaining sachets will be collected and counted. All families that have completed the intervention will be provided with a study closure package (including some rice and soap) as has been the standard goodwill practice of KHRC to participants from the communities. For those children who are anemic, based on their end-line hemoglobin assessment, an additional 60 sachets of iron-containing powdered fortificant will be provided. Providing iron to anemic children is not a safety issue in this case because they will be eligible for treatment according to the WHO statement on the use of iron in malaria endemic areas (3).

*d) Discontinuation of supplementation.* Supplementation will be stopped if any of the following is reported: admission to the hospital ward for >5 days; evidence of chronic diarrhea (defined as loose stools lasting >4 weeks); prolonged fever of unknown origin; emergence of any exclusion criteria after randomization. Prompt, daily disclosure by field workers of any concerns will be encouraged. If necessary, children will be referred to local physicians for treatment according to local standards. Reasons for stopping supplementation voluntarily will be recorded.

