##### Primary analysis

The primary outcome, incidence of malaria, will be compared between the two groups using Poisson regression. A 95% confidence interval for the ratio between the incidence in the iron group and the incidence in the placebo group will be calculated. The upper boundary of this confidence interval will be compared to the 10% tolerance limit. If it is lower, then non-inferiority can be concluded.

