##### Secondary analysis

Univariate Poisson regression with the same outcome will be used to evaluate associations with other variables: iron status at baseline, breast-feeding, age, gender and use of bed-net. These will then be introduced and re-evaluated in a multiple Poisson regression model, which will allow for adjusted group comparisons. Most importantly, by including the baseline iron status variable and the interaction with the main group variable, we can focus on the iron sufficient children that are receiving iron supplements and compare them against the others. The Poisson models will be validated by checking the model fit and for over-dispersion. Adjustments or transformations will be used if necessary.

The number of hospital admissions will be analyzed in a similar fashion, using Poisson regression. The parasite count outcome will be compared between the two groups, using a t-test. Univariate associations with other factors will be verified here as well, using t-tests, correlation coefficients and univariate regression.

Ultimately a multiple regression model will be developed, again for the purpose of adjusted comparisons between groups.

The normality of the data will be verified and, in the case of any departures, a log-transformation will be used and the data reanalyzed. If the log-transformation fails to achieve normality, a nonparametric alternative will be used instead. All statistical analyses will be carried out using SAS 9.1. The Analysis will be carried out on an intention-to-treat basis including all randomized children.

Upon the completion of the first intervention phase, an interim analysis will be performed by a Data and Safety Monitoring Committee (DSMC) as described above (primary analysis). The study will be stopped if the incidence of malaria is higher in one group.

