## 8. PROTECTION OF HUMAN SUBJECTS

### 8.1 Risks to Human Subjects

#### 8.1a Human Subjects Involvement and Characteristics

- Proposed involvement of human subjects
  - i. Studies using animals are not appropriate to answer the research questions posed in this proposal, namely to determine the impact of the provision of iron on the susceptibility to clinical malaria among infants and young children (6-24 months of age)

living in a high malaria burden area, using a powdered vitamin and mineral 'sprinkle' added to complementary foods.

- Characteristics of the subject population – number, age range, health status
  - i. Number: Approximately 930 in the intervention group and 930 in the control group
  - ii. Age: 6 – 24 months
  - iii. Health Status – generally healthy
- Inclusion/exclusion criteria for any subpopulation
  - i. Children to be included must meet the criteria described above. They must be free of clinical signs of infection (including malaria) at the time of enrolment. They must have plans to remain in the study area for the duration of the intervention. Informed consent must be freely given by a parent of the children enrolled for the study. Both boys and girls will be recruited without bias. Girl children will specifically be encouraged to participate, as appropriate.
  - ii. Children will be excluded if they fail to meet the inclusion criteria shown above.
- Rationale for involvement of special classes of subjects (e.g. children)
  - i. The highest malaria burden is in children in the first 3-4 years of life and the highest iron deficiency anemia burden is in the age range 6 – 24 months of age. Thus, we choose to include children who are at highest risk of anemia and malaria.
- List any collaborating sites where human subjects research will be performed, describe role of those sites and collaborating investigators in performing proposed research
  - i. The research field work will be conducted in northern Ghana, within the catchment area of the Kintampo Health Research Centre (KHRC). KHRC is one of three Ministry of Health Research Centres in Ghana.
  - ii. Research Ethics Board approval will be from two sources: the University of Toronto, the home institution of the PI and the Ghana Ministry of Health.
  - iii. The University of Toronto, Hospital for Sick Children PI will provide oversight of the project, while the co-investigator at KHRC will supervise all aspects of the field research.

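### The protocol judges non-inferiority on intention-to-treat alone, although missed doses and stopped sachets pull the rate ratio towards 1; it is also unclear whether an on-study malaria episode stops the sachets

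*Protocol*

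**What the plan says.** **Decision rule.** Section 5.5, Primary analysis: "The primary outcome, incidence of malaria, will be compared between the two groups using Poisson regression". Then: "The upper boundary of this confidence interval will be compared to the 10% tolerance limit". If it is lower, non-inferiority is concluded.

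**Population.** Section 5.5, Secondary analysis, final paragraphs: "The Analysis will be carried out on an intention-to-treat basis including all randomized children". No supporting population is named.

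**Exposure.** Section 5.2, Monitoring visits, draws on earlier studies: "the adherence to the use of the sachets is generally in the range of 70" to 98%. Used and unused sachets are counted at visits, and the remainder is counted at month 5.

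**Stopping sachets.** Section 5.2(d) lists hospital admission beyond five days, chronic diarrhoea, prolonged unexplained fever, and "emergence of any exclusion criteria after randomization".

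**What counts as an exclusion criterion.** The formal list in section 5.1 does not name malaria. The sentence after it says that children who are severely anaemic and/or "have symptoms of clinical malaria will be excluded from entry to the study". Section 8.1a says of enrolled children: "They must be free of clinical signs of infection (including malaria) at the time of enrolment", and adds: "Children will be excluded if they fail to meet the inclusion criteria shown above".

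**The concern.** In a superiority trial, dilution from non-adherence works against the sponsor's claim. In a non-inferiority test of safety it works for the claim: the less iron the iron group takes, the more alike the two groups look. Sections 2 and 3.3 link a finding of no adverse effect to possible scale-up of the product, so a false conclusion of safety is the costly error. The protocol fixes a population in which non-exposure helps the favourable result, and it does not require any second look.

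The stopping rule adds an uncertainty. Malaria is the primary outcome and is expected to be common. If field staff read the rule in 5.2(d) to include malaria, a large share of follow-up would be off sachets. If they read it by the formal list, almost none would be off sachets for that reason. The text allows both readings.

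**Working it through.** **Inputs.** Section 5.1 and Table 1 give a placebo rate of 3.44 × 0.75 = 2.58 per child-year, follow-up of T = 5/12 year, 843 children per group per season before inflation for loss, and a 15% increase as the difference of interest. Section 5.5 gives the limit of 1.10 and the 95% interval. Pooling both seasons (1,686 per group) is my assumption, shown for comparison.

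**The plan's own figure.** Person-years per group = (z_α + z_β)²(r0 + r1)/(r1 − r0)², with r0 = 2.58 and r1 = 1.15 × 2.58 = 2.967. At two-sided α = 0.025 (5% split over two tests) and 80% power this is (2.241 + 0.842)² × 5.547/0.387² = 352, against 351 stated. Then 351/(5/12) = 842, against 843, and 843 × 1.15 = 969, against 970. The inputs are therefore read as intended.

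**Chance of declaring non-inferiority.** With an intention-to-treat ratio r, P = Φ((ln 1.10 − ln r)/SE − 1.96), where SE = √(1/E0 + 1/E1). E0 = 843 × 2.58 × 5/12 = 906 expected episodes per season and E1 = 906r. With no dilution and a true ratio of 1.10, P = 2.5%.

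**Route 1: missed doses.** Assume that the excess risk is proportional to doses taken, so r = 1 + adherence × (R − 1) for a true ratio R. For R = 1.10:

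| Adherence | r | One season | Pooled |
|---|---|---|---|
| 98% | 1.098 | 2.7% | 2.8% |
| 84% (midpoint) | 1.084 | 5.0% | 6.5% |
| 70% | 1.070 | 8.7% | 13.3% |

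For example, at 70%: SE = √(1/906 + 1/970) = 0.0462, and Φ(0.0277/0.0462 − 1.96) = Φ(−1.36) = 8.7%.

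**Route 2: sachets stop permanently at the first malaria episode, and the iron effect stops with them.** This is one reading of 5.2(d), taken at its limit.

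- Placebo children with at least one episode: 1 − exp(−2.58 × 5/12) = 1 − exp(−1.075) = 65.9%.
- Share of person-time after stopping: 1 − 0.659/1.075 = 39% on placebo, and 41% to 43% on iron for R = 1.10 to 1.15.
- Intention-to-treat ratio: r = [(1 − e^(−R·r0·T)) + r0(T − t_on)]/(r0·T), with t_on = (1 − e^(−R·r0·T))/(R·r0).
- R = 1.15: t_on = 0.2391, so r = (0.7095 + 0.4580)/1.075 = 1.086.
- R = 1.10: t_on = 0.2444, so r = (0.6935 + 0.4446)/1.075 = 1.059. False non-inferiority is 12.9% per season and 21.5% pooled.
- R = 1.15: false non-inferiority is 4.6% per season and 5.8% pooled, against 0.2% and 0.04% undiluted.

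**Sensitivity of route 2 (true ratio 1.15).** If half the excess persists after stopping, r = 1.118. If half of first episodes lead to stopping, r = 1.118; if a quarter do, 1.134. With no carry-over, r is 1.112 at half the planned rate (1.29 per year, an assumption), 1.074 at 3.44 per year, and 1.043 at the local rate of 7 per year in section 4. If malaria does not stop sachets, r stays at 1.15.

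**The case against.** **The formal list omits malaria.** The wording that brings malaria in is tied to baseline or enrolment. Section 5.2(d) also sets thresholds for unexplained fever and length of admission, which would have little purpose if any febrile illness already stopped sachets. This stands: a reader might infer that the first malaria episode ends supplementation, but the text does not say so. What remains is ambiguity, because 5.1 and 8.1a use exclusion loosely and nothing exempts malaria from 5.2(d).

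**Counting repeat episodes does not contradict stopping sachets.** A reader might see a conflict with the tracking part of 5.2. There is none: episodes can be counted off sachets, and under intention-to-treat they should be.

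**The size is a worst case.** Route 2 needs permanent stopping at every first episode and no carry-over. Section 3.1 reports haemoglobin effects lasting up to six months after the intervention ends. A diluted ratio of about 1.09 is also not a pass, since the test uses the upper confidence limit. This stands, so route 2 is an upper bound.

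**Supporting populations are usually set in the analysis plan, and imperfect use is part of a policy question.** Both points are fair, and a plan not shown may add such a set. But this protocol itself states the population and the decision rule together, with no second condition.

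**The remedy has its own bias.** An on-supplement set selects after randomisation, and if malaria does stop sachets it cuts follow-up at the primary outcome. This also stands. It is why the set should be added to intention-to-treat and not replace it.

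**Conclusion.** The concern holds in a limited form. Section 5.5 rests a non-inferiority safety claim on intention-to-treat alone while the protocol expects incomplete use, and the direction of the resulting error favours the claim. From adherence alone, false non-inferiority at a true ratio of 1.10 lies between about 3% (98% adherence) and 9% (70%) per season, or 13% pooled at 70%. This assumes that the effect is proportional to doses taken, which the protocol does not establish.

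The stopping rule is ambiguous about the primary outcome. Its possible contribution runs from nothing, if malaria does not stop sachets, to about 13% per season and 21% pooled under the strictest reading. The document does not support the stronger inference that the rule as written does include malaria. The point deserves a change before the trial starts but does not invalidate the design.

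**What to change.** 1. In section 5.5, keep intention-to-treat and add a pre-specified on-supplement analysis: person-time up to stopping plus a short stated lag, with adherence taken from the sachet counts. Claim non-inferiority only if the upper limit of this analysis supports the intention-to-treat result. State that the set is open to selection after randomisation.
2. Reconcile sections 5.1, 5.2(d) and 8.1a so that 5.2(d) names the criteria it means and says whether an on-study malaria episode is one of them. Which rule applies is a clinical decision for the investigators.
3. State that follow-up and episode counting continue after sachets stop.

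**Cost.** Protocol wording and one further analysis of data already being collected. The non-inferiority claim becomes somewhat harder to reach.

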## 5.3 Analyses

Research Plan version 2  
February/2009

### *Laboratory and Clinical Analyses*

All laboratory analyses will be conducted at the Kintampo Health Research Centre by qualified laboratory technicians.

Screening for malaria will be performed using RDTs to help decide on treatment and blood smears for microscopy to provide counts. All clinical signs and symptoms will be interpreted using standardized 'case definitions' as described in previous studies (16, 54). For example, cerebral malaria (defined by a parasite count  $>5000/\mu\text{L}$  blood and a concurrent score of  $\leq 2$  on the Blantyre coma scale, with or without convulsions), pneumonia (defined by the presence of a cough or breathing difficulties, tachypnea, lower chest wall indrawing, and the appearance of consolidation or pleural effusion on a chest X-ray), diarrhea (defined by  $\geq 3$  loose or watery stools in the previous 24 hours), and dehydration (defined by lethargy, sunken eyes, and decreased skin turgor [ $>2$  seconds for skin to return following a skin pinch]) will be assessed in the hospital or health centre using standard procedures/methods. Severe malaria disease will be diagnosed based on symptoms and signs occurring at presentation or developing during admission according to generally accepted case definitions as have been used in all previous studies in Ghana. These 'case definitions' are available on request.

For identifying and analyzing cause-specific deaths or admissions to hospital, we will use exclusive categories to ensure that independent events are not classified more than once. As such, we will first allocate malaria related causes, then pneumonia and other infection related causes, and finally diarrhea and others.

Blood samples will be assayed for hemoglobin (Hb) using Hemocues (Mallinckrodt, USA). Plasma ferritin, CRP, zinc protoporphyrin and transferrin receptor will be assayed using standard methods, including internal and external reference standards. Since CRP is a measure of inflammation, blood samples from subjects with elevated CRP values ( $>8$  mg/L) will be excluded from further analysis (55). It should be noted however, that even in a malaria endemic area, albeit in school children (in Zanzibar), iron status assessment using these indicators may not be seriously influenced by malarial infection (4). Zinc protoporphyrin is a metabolic intermediate of the hemoglobin synthetic pathway which accumulates in red blood cells when iron supply is limited. It can be easily measured fluorometrically and is expressed as a ratio to heme (ZPP/H). In adults, ZPP/H correlates inversely with plasma ferritin across a wide range of ferritin concentrations (56), and is inversely related to the amount of stainable iron in the marrow (57). In adults (56, 58, 59) and children (60) ZPP/H has been shown to be more sensitive than the packed cell volume or hemoglobin concentration in detecting iron deficiency. It is particularly suited as a screening test because it is cheap, convenient (61) and can be carried out on a single drop of blood (62). ZPP/H ratios are expressed as  $\mu\text{g/g}$  hemoglobin (Hb) and plasma ferritin as  $\mu\text{g/L}$ . ZPP/H and plasma ferritin will be log transformed (to the base 10) before analysis to normalize the distribution, as both are usually positively skewed.

TfR and ZnPP are sensitive measures of iron-deficient erythropoiesis and have been used to define iron status in children in developing countries (63-67). TfR may have an advantage over SF because it is unaffected by the acute phase response (63, 68, 69). However, the specificity of TfR may be low because it can be increased by malaria (70), megaloblastic anemia due to vitamin deficiencies (71), and hemoglobinopathies such as sickle cell disease (72), hemoglobin H disease, and the thalassemias (73, 74). ZnPP has advantages of low cost and simplicity, but its specificity may be low as it also can be increased by malaria and other infections, chronic inflammation, and hemoglobinopathies (60, 63, 64, 75-77). To improve specificity, SF is often combined with TfR, ZnPP, or both (78). In the current protocol, we will include all three measurements in our assessment of iron status.

Zimmerman et al recently studied the use of serum transferrin receptor and zinc protoporphyrin as indicators of iron status in African children (Côte d'Ivoire). He determined the most sensitive and specific markers for iron status and their 'optimal' diagnostic cutoffs (TfR  $>9.4$  mg/L or ZnPP  $> 52$   $\mu\text{mol/mol}$  heme) after correcting for

inflammation (79). We plan to use these cutoffs to define iron status as iron replete and anemic, iron deficient and anemic, of iron replete and not anemic. Zimmerman defined anemia as a hemoglobin concentration below the WHO cutoff values (110 g/L) minus 10 g/L, and normal ferritin as  $> 30 \mu\text{g/L}$  (79). Several investigators have argued that a SF concentration  $>30 \mu\text{g/L}$  should be used to define adequate iron stores in developing countries with a high prevalence of infection (63, 80). Therefore, we have chosen a SF cutoff of  $>30 \mu\text{g/L}$  as being indicative of iron sufficiency.

To summarize: anemia will be defined as  $\text{Hb} < 100 \text{ g/L}$ ; IDA will be defined as  $\text{Hb} < 100 \text{ g/L}$  plus one of low ferritin ( $<30 \mu\text{g/L}$ ), high TfR ( $>9.4 \text{ mg/L}$ ) or ZnPP ( $>52 \mu\text{mol/mol heme}$ ); and iron deficiency will be defined as one of low ferritin ( $<30 \mu\text{g/L}$ ), high TfR ( $>9.4 \text{ mg/L}$ ) or ZnPP ( $>52 \mu\text{mol/mol heme}$ ). We recognize that infection and inflammation will confound the interpretation of SF, TfR, and ZnPP; thus we will exclude and/or adjust these indicators for those children who have signs of infection or inflammation, as defined by an elevated CRP concentration ( $>8 \text{ mg/L}$ ) (55, 81).

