Our secondary objectives are to determine the impact of this iron intervention on the *severity* of clinical malaria by documenting parasite counts and hospital admission rates, as well as differences in secondary complications of malaria infections, such as death, cerebral malaria, pneumonia, dehydration, and diarrhea. Although the current study is not powered to show causation between the intervention and the secondary outcomes, it is anticipated that the proposed research will help address the confusion that has been generated regarding the safe and appropriate use of iron supplements in high malaria transmission areas. If it is demonstrated that the provision of iron as a powder added to food does not have an adverse effect on malaria incidence and has a positive impact on anemia rates, then this type of iron delivery system can possibly be recommended for scale-up in Ghana and in other countries with a similar malaria burden. Conversely, if we

demonstrate adverse effects, especially in iron replete children, then further research is needed to identify inexpensive and non-invasive methods to screen children for anemia before iron is provided. **The long term goal of the proposed research is to develop new evidence to inform global policy and ultimately guide the implementation of programs to prevent and treat iron deficiency disorders in malaria endemic regions.** These goals coincide directly with the stated objectives of this RFA.

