#### *Global prevalence and impact of malaria*

Nutritional intervention programs have generally demonstrated that the provision of iron supplements can enhance child development (4, 5) and reduce the prevalence of severe anemia; however, there is some evidence to suggest that iron supplementation (in the form of syrups, drops or pills often provided in a post-prandial state) results in high levels of malaria parasitemia (6, 7), increased rates of malaria, as well as pneumonia and diarrhea (7-10). In contrast, the most recent systematic review (2002) does not generally support an increased risk of malaria attack rate or severity associated with iron supplementation (pooled OR significant for malaria + smear = 1.43 [1.08-1.91], but not significant when adjusted for baseline malaria smear = 1.24 [0.98-1.57]) (10). Clearly multiple factors contribute to the complex etiology of anemia in high malaria burden areas, but iron status and malaria infection are the strongest predictors of hemoglobin concentration (11). Recent research has suggested that haptoglobin might also influence hemoglobin levels in an environment of malaria-induced hemolytic stress. Research by Atkinson and colleagues suggest that the *Hp2/2* genotype is a risk factor for childhood anemia in malaria-endemic countries. The authors found that average hemoglobin levels fell over the malaria season, and children who had the *Hp2/2* genotype had the greatest drop compared to other children (11). These findings suggest that a child's haptoglobin type may be an important influence on whether that child gets anemia in areas where malaria is very common

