## **KHRC Priority Research Areas**

- Communicable diseases (CDs), particularly Malaria, TB and HIV/AIDS
- Sexual and Reproductive Health
- Maternal, Neonatal and Child Health
- Mental Health
- Non-communicable diseases (NCDs) such as hypertension and cancer
- Health Systems
- Using the DSS to track progress towards the Millennium Development Goals (MDGs) using indicators such as mortality levels, patterns and trends

Since 2003, [name] and his research teams at KHRC have characterized the epidemiology of malaria in the Kintampo area in the middle belt of Ghana (49-51). He has documented the incidence of malaria in children less than 5 years in this area as 7 attacks per child per year ([name] et al., in press). The transmission levels have been high throughout the year with an average inoculation rate of 269 infective bites per person per year ([name] et al., in press). [name] and his team of researchers are documenting the manifestations (both clinical and laboratory indicators) of severe and complicated malaria. Several antimalarials have been tested and evaluated in this area (52) and currently the most advanced malaria vaccine is being tested in Kintampo as one of several African countries. For more details on the KHRC laboratory and clinical facilities, please see pages 22-23 of this application (Resources Format Page).

The Kintampo Health Research Centre (KHRC) was awarded the 2008 Prince of Asturias Award for International Cooperation in recognition of its contribution to the fight against malaria in sub-Saharan Africa. The Prince of Asturias Foundation was formed by His Royal Highness, the Prince of Asturias, heir to the throne of Spain. It has conferred its awards since 1981. The awards are intended to acknowledge scientific, technical, cultural, social and humanitarian work carried out internationally by individuals, groups or in the categories of communication and humanities, social sciences, arts, letters, scientific and technical research, international cooperation, concord and sports.

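### The malaria-first exclusive allocation of admissions and deaths takes co-occurring cases out of the cause-specific pneumonia and diarrhea counts, and does so unequally by arm if iron raises malaria

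*Protocol*

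**What the plan says.** The rule is in protocol section 5.3, under Laboratory and Clinical Analyses. Its scope is stated at the start: "For identifying and analyzing cause-specific deaths or admissions to hospital". The plan then says "we will use exclusive categories to ensure that independent events are not classified more than once", and gives the order: "we will first allocate malaria related causes, then pneumonia and other infection related causes, and finally diarrhea and others". The same section gives pneumonia, diarrhea and dehydration their own case definitions, none of which excludes a child with parasites, and has them assessed in the hospital or health centre.

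Two other places say what these conditions are for:

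- Section 2 (Specific Aims) makes it a secondary objective to study "differences in secondary complications of malaria infections, such as death, cerebral malaria, pneumonia, dehydration, and diarrhea".
- Section 5.1 (Primary and Secondary Outcomes) lists as separate items "iv) hospitalization (from any cause) (v) death; (vi) pneumonia; (vii) diarrhea and dehydration".

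The protocol's only general definition of clinical malaria is in section 5.1: parasites at any density, together with measured fever or a report of fever in the preceding 48 hours. Section 5.2(c) has the parasite level determined in every admitted child. Section 5.3 does not say which definition decides that an admission or death is malaria related.

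**The concern.** A complication of malaria occurs together with malaria. A rule that gives each event a single cause, with malaria taken first, removes from the pneumonia and diarrhea categories the very cases that the section 2 objective asks about. The stated reason is to avoid classifying independent events more than once. That does not fit here: a child admitted with both conditions has had two outcomes that the protocol names separately.

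The overlap may be material. Section 4 reports an "average inoculation rate of 269 infective bites per person per year" at the site, and the general malaria definition has no density threshold.

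The rule can also act differently by arm. Section 5.1 hypothesises more malaria with iron, and section 3.1 cites evidence that iron supplements are followed by "increased rates of malaria, as well as pneumonia and diarrhea". If iron raises malaria, a larger share of iron-arm pneumonia and diarrhea admissions is moved to the malaria category. The cause-specific comparison could then show no excess, or an apparent reduction, in conditions that the trial names as outcomes.

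**Working it through.** The protocol gives no figure for this point, so there is none to reproduce. The check is on the direction and possible size of the misallocation.

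**Inputs**

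- *p*: the share of placebo-arm pneumonia (or diarrhea) admissions that also meet the malaria definition. It is not in the protocol. Assumed range 0.1 to 0.6.
- *r*: the iron/placebo ratio of that share. It is not in the protocol. The value 1.15 is borrowed from section 5.1, where 15% is the difference in malaria incidence held to be clinically significant. That is a different quantity, used here only for scale.

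**Formula**

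Under the exclusive rule only cases without malaria remain in the category: a fraction 1 − p in the placebo arm and 1 − r·p in the iron arm. Hence

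observed RR = true RR × (1 − r·p) / (1 − p).

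**Results with r = 1.15**

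| p | Removed, placebo | Removed, iron | Observed RR, true RR 1.00 | Observed RR, true RR 1.15 |
|---|---|---|---|---|
| 0.1 | 10% | 11.5% | 0.885/0.90 = 0.98 | 1.13 |
| 0.2 | 20% | 23% | 0.770/0.80 = 0.96 | 1.11 |
| 0.3 | 30% | 34.5% | 0.655/0.70 = 0.94 | 1.08 |
| 0.4 | 40% | 46% | 0.540/0.60 = 0.90 | 1.04 |
| 0.5 | 50% | 57.5% | 0.425/0.50 = 0.85 | 0.98 |
| 0.6 | 60% | 69% | 0.310/0.40 = 0.78 | 0.89 |

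**Sensitivity to r**

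- r = 1.00: the observed ratio equals the true ratio at every p. The only effect is that a share p of events is lost in each arm.
- r = 1.10: a true null reads as 0.99 (p = 0.1) to 0.85 (p = 0.6).
- r = 1.30: a true null reads as 0.97 (p = 0.1) to 0.55 (p = 0.6).

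**The case closest to the section 2 objective**

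Suppose iron raises pneumonia only as a complication of malaria. Take 100 placebo pneumonia admissions with p = 0.5: 50 with malaria and 50 without. If iron raises the malaria-associated ones by 15%, the iron arm has 57.5 + 50 = 107.5, a true RR of 1.075. The exclusive category compares 50 with 50 and shows 1.00. The same happens at any p, because the whole excess lies in the cases that the rule moves.

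**Where the moved events go**

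They enter the malaria-related category and remain in all-cause hospitalization and death. The admissions analysis in section 5.5 is a Poisson regression on the number of admissions without a split by cause, so it is unaffected.

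**The case against.** The strongest objection is scope. Section 5.3 states the rule for cause-specific deaths and hospital admissions. Pneumonia and diarrhea/dehydration are listed in section 5.1 apart from hospitalization and death, have their own case definitions, and are nowhere expressly placed under the hierarchy; home visits also collect morbidity. On this reading outcomes (vi) and (vii) may already be counted whatever the smear shows. This stands in part: the text does not settle it. But section 5.2(c) orders the tests for these conditions on admission, and the section 5.3 pneumonia definition needs a chest X-ray, so much of their ascertainment falls within the rule's reach. Diarrhea reported at home may not.

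A single-cause hierarchy is also a legitimate way to build a table that adds up, and section 2 concedes that the study is not powered for the secondary outcomes. Both are fair. They limit the weight of the point but do not remove the conflict with the section 2 objective. A supplementary multiple-cause count could stand in an SAP that is not at hand, and its absence from the protocol is no fault; the point is the rule that the protocol itself fixes.

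Three stronger readings are tempting, and the protocol does not support them:

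- *The cases vanish from the safety outcomes.* They do not. They leave only the cause-specific pneumonia or diarrhea count and, if iron raises malaria, add to the iron arm's malaria count.
- *Every child with parasites is coded as malaria.* The general definition also requires fever or reported fever, and section 5.3 refers to case definitions from previous studies that are not reproduced. Applying the section 5.1 definition at this step is an inference.
- *Diarrhea loses most because it comes last.* Loss depends on overlap, which is not given. The diarrhea definition does not require fever, so some cases would not meet the malaria definition.

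**Conclusion.** The point holds for the cause-specific admission and death categories. The protocol fixes an exclusive, malaria-first rule for analysing them. Followed as written, it removes co-occurring pneumonia and diarrhea/dehydration cases from those counts, against the objective in section 2 and the separate listing in section 5.1. If iron raises malaria, the distortion favours iron.

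The direction follows from the rule; the size does not. Under the assumed overlaps and r = 1.15, a true null reads anywhere from nearly unbiased to roughly a fifth too low, and there is no bias in the ratio if overlap is equal by arm. A particular figure such as 0.85 should not be read as an estimate for this trial. The primary outcome, all-cause hospitalization and all-cause death are untouched. This is a worthwhile correction to secondary outcomes, not a threat to the main conclusion.

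**What to change.** Amend section 5.3 in three ways:

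1. Define malaria related for the allocation of admissions and deaths, either by pointing to the section 5.1 definition or by stating another.
2. State that secondary outcomes (vi) and (vii) are counted whenever the section 5.3 case definition for pneumonia, diarrhea or dehydration is met, whatever the smear shows, and compare the arms on those counts.
3. Keep the exclusive hierarchy only as a descriptive breakdown of all-cause admissions and deaths.

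The observed ratio then no longer depends on overlap with malaria, and no co-occurring case is dropped. The case definitions are already to be assessed in the hospital or health centre, so no new data are needed and the cost is wording. The downside is that cause-specific counts no longer add up to the all-cause total, which a table footnote should say.
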